#### Study Part B

Based on the results of study part A, the second part will consist of a multicenter, two-armed, randomized-controlled parallel group trial. Participants in the intervention group (IG), for a period of 4 weeks, will receive online workouts with video live-streaming using the appropriate software (e.g., Zoom, Zoom video communications, San Jose, California, USA; BlackBoard, Washington, DC, USA). Duration, frequency, and contents will be selected balancing (a) the needs of the population as indicated via the ASAP questionnaire and (b) scientific recommendations for exercise prescription. For example, the minimum training frequency will be once per week and minimum duration will be 10 min (21). To allow a higher degree of standardization between the countries, the instructors will be provided with modifiable demo workouts exhibiting different content-related focuses (e.g., strength, endurance, postural control/balance, cognition, relaxation), which can be individually adapted. The control group (CG) will not receive an intervention and is instructed to complete the outcome assessments (see below). Randomization (1:1 ratio) will be performed using a software algorithm of the online database used for survey delivery (Soscisurvey, Soscisurvey GmbH, Munich, Germany). To allow concealed group allocation, the participants will be automatically informed by the system about allocation upon survey completion at baseline.

A two-fold approach is used for recruitment. Firstly, upon completion of the ASAP questionnaire (study part A), each participant will be informed about the opportunity to participate in the subsequent intervention trials (Study Parts B and C). Second, the same recruitment strategies used for the initial survey (social media advertising and promotion via associations and societies) will be used to enhance recruitment.

#### Study Part C

Study Part C adopts a controlled crossover design. Following completion of the post-measurements of study Part B, the participants of both groups (intervention and control) will receive access to an online database of recorded workouts with contents similar to Part B. All contents can be freely used for four additional weeks.

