## Abstract

**Introduction:** The worldwide spread of the novel coronavirus (SARS-CoV2) has prompted numerous countries to restrict public life. Related measures, such as limits on social gatherings, business closures, or lockdowns, are expected to considerably reduce the individual opportunities to move outside the home. As physical activity (PA) and sport participation significantly contribute to health, this study has two objectives. The objectives of this study are to assess changes in PA and well-being since the coronavirus outbreak in affected countries. Additionally, we will evaluate the impact of digital home-based exercise programs on PA as well as physical and mental health outcomes.

**Method:** A multinational network trial will be conducted with three planned phases (A, B, and C). Part A consists of administering a structured survey. It investigates changes in PA levels and health during the coronavirus outbreak and measures the preferences of the participants regarding online training programs. Part B is a two-armed randomized-controlled trial. Participants assigned to the intervention group (IG) will complete a digital 4-week home exercise training (live streaming via internet) guided by the survey results on content and time of program. The control group (CG) will not receive the program. Part C is 4-week access of both CG and IG to a digital archive of pre-recorded workouts from Part B. Similar to Part A, questionnaires will be used in both Part B and C to estimate the effects of exercise on measures of mental and physical health.

**Results and Discussion:** The ASAP project will provide valuable insights into the importance of PA during a global pandemic. Our initial survey is the first to determine how governmental confinement measures impact bodily and mental well-being. Based on the results, the intervention studies will be unique to address health problems potentially arising from losses in PA. If proven effective, the newly developed telehealth programs could become a significant and easy-to-distribute factor in combating PA decreases. Results of the study may hence guide policy makers on methods to maintain PA and health when being forced to restrict public life.

**Study Register:** DRKS00021273.

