## Materials and Methods

### Ethical Standard and Study Design

The ASAP (**A**ctivity and health during the **SA**rs-CoV2 **P**andemic) project (Figure 1) consists of a structured, multinational cross-sectional survey (study Part A), a two-armed, randomized-controlled, multicenter parallel group trial (study Part B), and a controlled multicenter crossover trial (study Part C). It will be conducted according to the Guidelines of Good Clinical Practice and adhering to the Declaration of Helsinki. This study protocol reports according to the Standard Protocol Items: Recommendations for Interventional Trials (SPIRIT) guidelines (14). Approvals are obtained from the study center's review board (Ethics committee of the faculty of psychology and sport sciences at Goethe-University Frankfurt) as well as from all universities actively included into participant recruitment. The intervention parts of the study have been prospectively registered at the German Registry of Clinical Trials (DRKS00021273).

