### Data Processing and Statistics

All datasets will be analyzed using intention-to-treat. The findings from the ASAP questionnaire (Study Part A) will be descriptively reported and presented using appropriate measures such as mean ± standard deviation or median and interquartile range depending on distributions and scales of measurement. Additionally, the significance of variable associations (e.g., between physical activity levels and markers of well-being) will be examined using correlation and regression analyses.

To estimate the risk of non-response bias, wave analyses will be conducted according to Lewis et al. (26). Specifically, the responses of the first 10% percent of the participants (early responders) will be compared to those of the last 10% (late responders) by means of inferential statistics. The rationale behind this is that early responders are assumed to be more motivated than late responders which can be compared to non-responders. Hence, if the wave analyses do not provide significant findings, absence of non-response bias is concluded.

For study Parts B and C (randomized, controlled trial/controlled crossover trial), a prospective meta-experiment approach will be applied (27). For each country, the mean pre-post-differences between-groups including 95% confidence intervals (95% CI) will be calculated at the different time points. An a priori sample size calculation using an algorithm specifically designed to account for between-site variance in multi-center trials was performed (28). When achieving a sample size of *n* = 544 with an included drop-out rate of 20%, the trial will have 80.3% power to detect pre-post-differences with a minimal effect size (Cohen's *d*) of 0.25 at an alpha level of 0.05. To account for potential between-center variance, the data collected in each country will be pooled using a random-effects model (29). This leads to an aggregated effect size (weighted mean differences) demonstrating the overall effectiveness of the intervention while the different countries can still be compared by means of inspecting the 95% CI's. Heterogeneity between countries will be quantified by means of the *I*^2^ index (30). To further explore its potential sources (e.g., country, age, sex, baseline physical activity), a meta-regression with continuous and factorial independent variables will be performed (31).

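### Part C is labelled a controlled crossover, but both groups receive the archive together, so its between-group contrast does not estimate the archive's effect

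*Protocol article*

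**What the plan says.** Two sections of Materials and Methods fix the label. Ethical Standard and Study Design describes "a controlled multicenter crossover trial (study Part C"), and Study Part C repeats it: "Study Part C adopts a controlled crossover design". The Outcomes section also refers to T6 to T8 as the crossover study.

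The described access is different. The Study Part C section says that "the participants of both groups (intervention and control) will receive access to an online database of recorded workouts with contents similar to Part B", and gives the start as "Following completion of the post-measurements of study Part B". The Abstract agrees: "Part C is 4-week access of both CG and IG to a digital archive of pre-recorded workouts from Part B". In Part B, IG has four weeks of live-streamed workouts and CG has none.

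On analysis, Data Processing and Statistics says: "For study Parts B and C (randomized, controlled trial/controlled crossover trial), a prospective meta-experiment approach will be applied". It then specifies, for each country, the between-group difference in pre-post change at the various time points. These are pooled by a random-effects model, and the pooled value is read as showing how effective the intervention is overall. On purpose, the Abstract says that "questionnaires will be used in both Part B and C to estimate the effects of exercise on measures of mental and physical health", and the Discussion says that both intervention parts will measure how effective the digital programs are.

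**The concern.** A crossover estimates a treatment effect because participants, or groups in the same period, are seen both with and without the treatment in exchanged order. Here IG never moves to the control condition, and during Part C everyone has the archive. CG does not move to IG's Part B treatment either, because it receives recorded rather than live workouts. The label therefore promises an inference that the described design cannot give.

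This matters because the article attaches an analysis and an effectiveness claim to Part C. A reader who takes the label at face value would treat a T6 to T8 group difference as evidence about recorded workouts, and the absence of one as evidence against them. Neither follows. The Abstract says that the results may guide policy makers, and a freely distributed archive is the kind of program on which they would want an answer.

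**Working it through.** The plan gives no numerical claim specific to Part C, so there is no figure to reproduce on this point. The check is the algebra of the planned contrast. The only number taken from the plan is d = 0.25, from the sample size paragraph, used as an illustrative size.

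**1. Sequences, from the Study Part B and Study Part C sections**

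| Group | Part B (T1 to T5) | Part C (T6 to T8) |
|---|---|---|
| IG | live-stream | archive |
| CG | nothing | archive |

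The Part C column is the same for both groups.

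**2. Notation, in SD units**
- b: live-stream effect at T5
- r: share of b still present at the Part C time point
- aIG, aCG: archive effect in each group
- m: change since T1 that is common to both groups (calendar time, changing restrictions)

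**3. Planned contrast, change from T1**

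IG: m + r·b + aIG. CG: m + aCG.

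Difference = r·b + (aIG − aCG).

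Randomisation removes m. If aIG = aCG, the archive term is zero whatever the archive achieves.

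**4. Same contrast, change from T5**

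The article does not say which time point is the pre value for Part C. If it is T5, the difference = (r − 1)·b + (aIG − aCG). The archive term again cancels when the effects are equal.

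**5. Numbers with b = 0.25; r, aIG and aCG are assumptions**

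| r | aIG | aCG | From T1 | From T5 |
|---|---|---|---|---|
| 1 | 0 | 0 | 0.25 | 0 |
| 1 | 0.25 | 0.25 | 0.25 + 0 = 0.25 | 0 |
| 1 | 0 | 0.25 | 0.25 − 0.25 = 0 | −0.25 |
| 0 | 0.25 | 0.25 | 0 + 0 = 0 | −0.25 |
| 0.5 | 0 | 0.25 | 0.125 − 0.25 = −0.125 | −0.125 − 0.25 = −0.375 |

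Rows 1 and 2 are decisive: a useless archive and one worth 0.25 SD in both groups give identical contrasts. Rows 3 and 5 show what differential response does.

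**6. Range**

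With r from 0 to 1, aCG from 0 to 0.25 and aIG from 0 to aCG, the contrast runs from −0.25 to +0.25 measured from T1, and from −0.50 to 0 measured from T5.

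**7. The alternative within CG**

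CG's change from T5 is aCG plus whatever change occurs over time in that period. It describes the archive period but has no concurrent comparison, and restrictions may be changing at the same time.

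**The case against.** The strongest defence is that Part C is a one-way or delayed-access design, loosely named. CG does move from no intervention to an intervention. The randomised comparison continues through T6 to T8 as live-stream-then-archive versus nothing-then-archive, which is a legitimate contrast. The article is open that both groups get the archive, and the Discussion explains that offering it to CG is meant to limit withdrawal. No sentence says that a T6 to T8 difference will be read as archive versus no archive. Exact time-point contrasts can be left to a fuller document.

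Much of this stands. It would be wrong to call Part C simply uncontrolled, because the randomised early-versus-delayed comparison persists. The Abstract never uses the crossover label and needs no relabelling.

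What does not stand is that nothing needs correcting. The article itself fixes the crossover label, applies the between-group contrast to Part C, and claims effectiveness from both parts. A later analysis plan can name the estimand, but it cannot supply an archive-free group. The Discussion's plan to tailor some workouts to CG feedback creates no control either; it makes equal archive effects less safe to assume.

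**Conclusion.** The point holds as a mismatch between label, design and claim. Part C exchanges no treatments and has no concurrent archive-free group, so the planned between-group difference does not estimate the archive's effect. It equals the retained live-stream effect plus any difference in archive response between the groups. This is structural and depends neither on the sample size nor on the assumed values. The illustrative sizes (0.25 or 0 from T1 with a fully retained 0.25 SD effect) do depend on them, and on additive effects.

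A reader might infer that the plan reverses the sign of the archive's effect. The documents do not support that as a general statement. With equal archive effects the contrast from T1 is uninformative about the archive, not reversed. A negative value from T1 arises only if CG gains more from the archive than IG retains and adds. Negative values from T5 need fading of the live-stream effect or a larger archive response in CG, and the article does not name T5 as the reference. Nor does it state a decision rule that would classify the archive as effective or ineffective. The Part B randomised comparison is untouched.

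**What to change.** - In Ethical Standard and Study Design, Study Part C, Outcomes, and Data Processing and Statistics, replace the crossover label with an open-access extension of the randomised trial, with delayed access for CG.
- Define the T6 to T8 between-group difference in change from T1 as live-stream-then-archive versus delayed archive, that is, persistence or early versus delayed start.
- Report CG's change from T5 as descriptive and without a concurrent control.
- In the Abstract, Data Processing and Statistics, and the Discussion, limit the effectiveness claim to the Part B randomised comparison.

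The cost is wording and the naming of one contrast. The Part C claim becomes weaker. Nothing changes for participants, data collection or Part B.

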### Outcomes

As indicated above, the ASAP questionnaire represents the outcome of interest for study Part A. For study Parts B and C, eight assessments are planned: at baseline prior to the RCT (T1), as well as weekly during the RCT (T2–T5) and the crossover study (T6–T8). Each survey will include an assessment of basic information (e.g., sex and age) and brief questions assessing general psychological and physical well-being. Additionally, a battery of questionnaires will be applied. The components were chosen based on both, thorough psychometric evaluation and the availability of translation and cross-cultural validation for the languages used. Implemented tools include the WHO5 scale for mental well-being (16, 17), generalized anxiety disorder scale-7 [GAD-7, (22)] for impulsiveness and anxiety, the MOS 12-item scale for sleep quality (23), the self-concordance scale (24) for exercise motivation and the Chronic Graded Pain Scale (25) for pain. In addition to the intervention effects, data on acceptance and adherence will be collected by means of documenting attendance at each workout offered in study Part B as well as by means of asking for the frequency of database use in study Part C (T4 assessment).

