Some methodological considerations are needed. As home-exercise may become an important method to maintain PA during future confinements, it will be particularly interesting to study adherence. It has been reported that the feeling of being supported and the possibility to contacting the provider may facilitate compliance (47). As our exercises in study part A will be live-streamed and the participants can interact with the instructors, we believe this can improve training frequency compared to traditional home-exercise programs. Compliance will also be of importance in our CG. As it does not receive an intervention, participants may withdraw from the study. We chose two strategies to counteract this. Firstly, we offer them free database use in study Part B and thus, any participant enrolled will have a PA intervention. Secondly, the CG participants will be actively motivated to express their preferences regarding the video-database and, using their feedback, some workouts will be specifically tailored for them. Besides compliance, another issue relates to outcome assessment. We decided to use questionnaire assessments in both study parts, which is congruent with the objective to measure and improve subjective well-being and allows the achievement of large sample sizes. However, regarding PA assessments, it should also be noted that most persons tend to overestimate the own activity levels and that the recall of moderate-intensity activities is less precise than that of vigorous activities (48).

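### The question on Part C archive use is placed at T4, before the archive opens, and only three weekly assessments are planned for a four-week Part C

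*Protocol article*

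**What the plan says.** The Outcomes section gives the schedule for both intervention parts: "For study Parts B and C, eight assessments are planned", distributed as "at baseline prior to the RCT (T1), as well as weekly during the RCT (T2–T5) and the crossover study (T6–T8").

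The Study Part B section sets the length of the randomised period: "Participants in the intervention group (IG), for a period of 4 weeks, will receive online workouts".

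The Study Part C section says when the archive opens and to whom: "Following completion of the post-measurements of study Part B, the participants of both groups (intervention and control) will receive access to an online database". It then gives the length: "All contents can be freely used for four additional weeks". The Abstract and the Figure 1 legend agree on four weeks, and the legend also puts access after the trial.

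For adherence, the Outcomes section names two measures. In Part B, attendance is recorded at every workout. In Part C, participants are asked how often they used the database, with the time point given in brackets: "asking for the frequency of database use in study Part C (T4 assessment").

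The Discussion, explaining how controls will be kept in the study, says "we offer them free database use in study Part B". It also attaches the live-streamed sessions to Part A.

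**The concern.** There are two timing conflicts in the article's operative text.

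First, the only time point stated for the Part C usage item falls before Part C begins. A participant answering at T4 has had no archive to use. The answers would be blank, zero or a misreading of the question, and none of these measures Part C use. Since archive content is used freely in Part C, this self-report is the only stated measure of how much exercise participants took from it. Without it, a Part C result could not be read against exposure.

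Second, weekly assessment and a four-week period together imply four assessments in Part C, as in Part B, but three are listed. The Data Processing and Statistics section calculates between-group differences in change at each time point. What the last Part C contrast means, after three weeks of access or after four, therefore depends on where T8 falls, and the article does not say.

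**Working it through.** **Inputs**

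- Assessments in Parts B and C: 8 (Outcomes).
- Allocation: T1 before the trial, T2 to T5 weekly in Part B, T6 to T8 weekly in Part C (Outcomes).
- Length of Part B: 4 weeks (Study Part B). Length of Part C: 4 weeks (Study Part C).
- Archive access: after the Part B post-measurements, for both groups (Study Part C).
- Time of the usage item: T4 (Outcomes).

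**Reproducing the stated total.** 1 (T1) + 4 (T2 to T5) + 3 (T6 to T8) = 8. This agrees with the article, so the total is consistent with its own breakdown. The conflict is with the four-week length of Part C.

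**Position of T4.** Put T1 at week 0 with weekly spacing, so that assessment k falls at week k − 1:

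| Assessment | T1 | T2 | T3 | T4 | T5 | T6 | T7 | T8 |
|---|---|---|---|---|---|---|---|---|
| Week | 0 | 1 | 2 | 3 | 4 | 5 | 6 | 7 |

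T4 falls at 4 − 1 = week 3. T5, the last Part B assessment, falls at week 4 and is taken here as the post-measurement that precedes archive access. The conclusion does not depend on the exact weeks: T4 comes before T5, T5 is itself a Part B assessment, and access follows the Part B post-measurements. Under any dating of T2 to T5, T4 precedes access.

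**Coverage of Part C.** Part C runs from week 4 to week 4 + 4 = week 8.

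- Weekly assessments needed to cover it: 4. Planned: 3. Uncovered: 4 − 3 = 1 week, or 1/4 = 25%.
- Total for weekly coverage of both parts: 1 + 4 + 4 = 9, against the 8 planned.
- If spacing continues from T5, T6 to T8 fall at weeks 5, 6 and 7, and the end of Part C (week 8) is not measured.
- If T8 is set at the end of Part C, T6 to T8 fall at weeks 6, 7 and 8. The end is measured, but there is a two-week gap after T5 and no assessment at week 5.

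Both readings satisfy three weekly assessments in Part C. The article does not choose between them.

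**The case against.** The strongest reply is that T4 is a labelling slip. The sentence names Part C use as its object, every description of the archive in the Methods puts access after Part B, and anyone building the questionnaires might well notice. That is probably right about the intention, and it means a loss of all usage data is not certain. It does not repair the text: the bracketed T4 is the only time point given, and a questionnaire built from the article would carry the item in the wrong survey. Nor is this a case of an article leaving detail to a fuller document, because the article states labels, counts and intervals that do not fit together.

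A second reply is that eight assessments look deliberate, since the total and its breakdown agree, and that no passage names the end of Part C as a key time point. This stands in part. Nine assessments are not required, T6 to T8 still supply Part C outcome data, and a well-placed T8 would serve. What remains is that one week in four has no assessment and the placement is not stated.

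A reader might infer more from the Discussion, namely that controls get the database during Part B and that the randomised contrast is therefore ambiguous. The documents do not support this. The Abstract and the Study Part B section say controls receive no programme in that part, the Study Part C section puts access afterwards, and the same Discussion paragraph repeats that controls receive no intervention. Its part labels are shifted by one (A for the live-streamed part, B for the database part), which is a clerical error.

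A reader might also take the Discussion's special interest in adherence as referring to the archive. It refers to home exercise in general and goes on to the live-streamed sessions, for which attendance is recorded at each Part B workout.

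**Conclusion.** The point holds in two parts of different strength.

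The T4 placement is wrong as written. It rests only on the order of the assessments and on access following Part B, both of which the article states. If the item is asked at T4 and nowhere else, none of the Part C usage data would be valid.

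The coverage gap is one of four Part C weeks (25%). That the end of Part C goes unmeasured, with the last outcome at week 7 instead of week 8, is tempting to state as fact. It follows only if T6 comes one week after T5, and the article gives no calendar weeks for T6 to T8.

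The randomised comparison in Part B, served by T1 to T5, is unaffected by either part. The problem is confined to the measurement of Part C, but it lies in the operative Outcomes text and should be corrected there.

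**What to change.** 1. In the Outcomes section, replace T4 as the time of the archive-use question with the Part C assessments: T6 onward, including the last one, worded so that together they cover the whole access period.
2. State when T6, T7 and T8 fall relative to the opening of the archive. Then either set T8 at the end of Part C week 4 and give the resulting spacing, or keep weekly spacing from T5 and add a T9 at that point. With a T9, change the total from eight to nine.
3. In the Discussion, correct the part labels for the live-streamed sessions and for control-group database access so that they match the Study Part B and Study Part C sections.

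The cost is one item moved, a few words of text and, if T9 is chosen, one extra short online questionnaire per participant. Setting T8 at the end of Part C adds no questionnaire but leaves the first week of Part C without its own assessment, so the usage question at T6 would need to look back over two weeks.
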